# Studying feasibility and effects of a two-stage nursing staff training in residential geriatric care using a 30 month mixed-methods design [ISRCTN24344776]

**DOI:** 10.1186/1472-6955-10-10

**Published:** 2011-05-31

## Abstract

**Background:**

Transfer techniques and lifting weights often cause back pain and disorders for nurses in geriatric care. The Kinaesthetics care conception claims to be an alternative, yielding benefits for nurses as well as for clients.

Starting a multi-step research program on the effects of Kinaesthetics, we assess the feasibility of a two-stage nursing staff training and a pre-post research design. Using quantitative and qualitative success criteria, we address mobilisation from the bed to a chair and backwards, walking with aid and positioning in bed on the staff level as well as on the resident level. In addition, effect estimates should help to decide on and to prepare a controlled trial.

**Methods/Design:**

Standard basic and advanced Kinaesthetics courses (each comprising four subsequent days and an additional counselling day during the following four months) are offered to n = 36 out of 60 nurses in a residential geriatric care home, who are in charge of 76 residents. N = 22 residents needing movement support are participating to this study.

On the staff level, measurements include focus group discussions, questionnaires, physical strain self-assessment (Borg scale), video recordings and external observation of patient assistance skills using a specialised instrument (SOPMAS). Questionnaires used on the resident level include safety, comfort, pain, and level of own participation during mobilisation. A functional mobility profile is assessed using a specialised test procedure (MOTPA).

Measurements will take place at baseline (T0), after basic training (T1), and after the advanced course (T2). Follow-up focus groups will be offered at T1 and 10 months later (T3).

**Discussion:**

Ten criteria for feasibility success are established before the trial, assigned to resources (missing data), processes (drop-out of nurses and residents) and science (minimum effects) criteria. This will help to make rational decision on entering the next stage of the research program.

**Trial Registration:**

Current Controlled Trials ISRCTN24344776.

## Background

The daily duties of the geriatric nurses include many tasks including patient transfer. They also spend 36% of their working time in awkward postures [1]. This leads to physical strain, especially in patient transfer situations and nurses exhibit a high risk of developing musculoskeletal disorders, particularly in the back. In Germany 25.5% of the absenteeism of nurses in inpatient care is due to musculoskeletal disorders [2].

With increasing age immobility or even a bedridden state can ensue [3]. Due to the limits or lack of personal independence, the subjective well-being is restricted [4]. If a person is moved without being able to participate in the action, a feeling of helplessness is likely to arise or the person is pushed into an even worse level of disability. This means that the functional disability of the patient appears greater than it really is because of the deterioration in their physical or psychological condition [5,6]. This induces a feeling of helplessness and the patient does not know, as a result, which abilities they still really have command over [7]. The development and improvement of movement competence can influence positively the patient's well-being and health [8]. Fortunately, movement competence can also be improved even in old age [9].

Kinaesthetics, a care conception developed by Hatch and Maietta [10], aims to increase nurses' movement support skills relating to residents' daily activities and offers advantages both for nurses and residents. In order to implement this conception into practice, a training-on-the-job approach is favoured.

In the present paper, we

• introduce Kinaesthetics and show the lack of research evidence for the benefits of Kinaesthetics in geriatric care

• conclude that there is need for a strict and multi-step research programme, that considers complexity of this kind of intervention,

• describe the study protocol of the first trial in our programme, a pilot in order to check feasibility of a training programme for nurses as well as feasibility of learned skills implementation for nurses and for residents in clinical practice.

### Introduction to Kinaesthetics and review of effectiveness studies

#### The Kinaesthetics conceptual framework

Kinaesthetics is a care concept for human movement, which describes and analyses the fundamental nature of human movement with regard to self-control, functioning and health development. The theoretical bases are to be found in behavioural cybernetics, human psychology and various directions and styles of modern dance [10]. The founders of Kinaesthetics are Dr. L. Maietta and Dr. F. Hatch, USA, who first used Kinaesthetics with students who were interested in their own movement skills. The core of Kinaesthetics is the communication and interaction between humans which is carried out while moving [10]. This human interaction is considered under six concepts; interaction, functional anatomy, human movement, human functions, effort expended as a means of communication, and the environment. The sub-themes of the concepts allow a deeper analysis into different aspects of movement. Each of these concepts is present in every interaction and they can be used for a systematic analysis of human movement resources (Table 1) [10].

**Table 1 T1:** The concepts of Kinaesthetics

Main concepts	Sub-themes
1 Interaction	Senses (visual, auditory, taste, smell, tactile, kinaesthetic)
	Movement elements (time, effort, space)
	Types of interaction (mutual, serial, unilateral)
2 Functional anatomy	Bones and muscles
	Masses and spaces
	Orientation to one's own body
3 Human movement	Postural and transport movement
	Parallel and spiral movement patterns
4 Effort	Pulling and pushing
5 Human functions	Simple human functions (positions)
	Complex human functions (locomotion and movement in place)
6 Environment	Movement supporting and restricting environment

#### Conception for nurse education in Kinaesthetics

The purpose of Kinaesthetics training is to give nurses the fundamental understanding of natural human movement and of its meaning with regard to human existence, perception of one's own body, environment and functioning in daily life. Through this understanding the nurses should develop their own movement competences.

Movement competence is defined as the ability to use one's own movement for solving motor, cognitive or social challenges with motion and to create optimal situations [9]. Ideally, it uses all of the internal and external resources for motor situations in daily life such as in their job and leisure time. Internal resources are the motor abilities and skills, e.g. physical condition, coordination, cognition and constitution. External resources are the potential of the environment such as devices or the social environment [11]. Nurses are more able to work in a resource-orientated manner, to perform different resident movement tasks with ease, to support the patient's active participation towards their own locomotion and to increase the patient's perceptions of their own body and environment. The methods of teaching are interpersonal and interactive.

In Kinaesthetics courses, nurses learn first to understand each concept in their own body. They learn to recognise what happens in their own body while moving themselves. This is a precondition for their understanding of the movement of other people. Secondly, they learn to move other people by using their experiences of each concept. Thirdly, they use Kinaesthetics concepts in different patient situations. The workbook is used to support the cognitive learning.

#### Studies on the effects of Kinaesthetics for the nursing staff

There are only few studies of the effects of Kinaesthetics on the nursing staff. One study in Finland investigated the impact of Kinaesthetics on the physical strain of the nurses in one health care centre taking care of elderly surgical and medical patients [12]. The aim of this study was to show the change in the physical strain on back and shoulder muscles in 12 nurses who swapped the usual transfer technique for the new method, Durewall^® ^(a transfer technique from Sweden) and Kinaesthetics 83 transfers (bed-wheelchair/wheelchair-bed) were videotaped (25 before training, 28 after the first training and 30 after the second training). During the transfers, the nurses' activity of m. trapezius and m. erector spinae were measured on both sides with a portable EMG.

Furthermore, experts in Kinaesthetics evaluated the nurses' individual performance and learning in patient transfer tasks and the patient participation in locomotion activities from the videotapes. For this purpose a newly developed instrument, SOPMAS (Structure of The Observed Patient Movement Assistance Skill) was used. It covers the following ergonomic and Kinaesthetics items: interaction, patient's movement, nurse's posture and movements as well as environment and auxiliary devices. The rating scale ranged from 1 = no skills to 5 = very good skills.

The results indicated, that the nurses could develop their own movement competence and that the mobilisation with Durewall^® ^or Kinaesthetics reduced the physical load by 50%. The EMG results correlated significantly with the SOPMAS results, which means, that a higher SOPMAS score signifies a decline in physical strain [12].

In a prospective, descriptive comparative study, Burns and Sailer investigated whether Kinaesthetics can positively influence the discomfort in neck and lumbar spine by nurses in a neurological clinic [13]. In the intervention group there were 65 nurses from 6 wards. In the control group there were 60 nurses from 6 wards. The answers from the questionnaire showed that the intervention group which was trained in Kinaesthetics had less back pain than the control group. These results indicate that training in Kinaesthetics could reduce the back pain in nursing staff.

#### Studies on the effects of Kinaesthetics for the elderly residents

In the study of Tamminen-Peter (2005) patients were asked for their safety, control and comfort during the mobilisation with a bipolar scale from -4 to +4. All of these three quality indicators were found to be significantly better by the mobilisation with the new methods (Durewall and Kinaesthetics) [12].

One case study examined if a movement support based on Kinaesthetics furthers the development and improvement of body awareness, movement abilities and functional independence of elderly nursing home residents [14]. Two elderly nursing home residents, who showed a strong dependence (Barthel index II; 20-60 points) after a stroke, demonstrated a clear improvement in information understanding, body perception, and movement abilities. Functional independence measured by Barthel index increased in case A from 30 to 40 points and, case B from 55 to 95 points. The results indicate that movement support based on the principles of Kinaesthetics, if used consistently, continuously and in a manner adapted to the situation of the person requiring assistance, could increase the body perception, movement abilities, and the functional independence of patients of advanced age.

Burns and Sailer studied patient's independence in the activity of daily-life movement and how the patients experienced the concept of Kinaesthetics [13]. Twelve patients were interviewed in a semi-structured interview. The result was that the patient experienced a higher feeling of safety and independence. It is not clear, however, if it was the concept of Kinaesthetics or the greater attention of the nurses which influenced the results with regard to increased feeling of safety and greater independence on the part of the patients. One further limitation was the fact that the nurses were not all equally adept in the use of the concept of Kinaesthetics.

On the whole, health care organisations are investing heavily in staff training in Kinaesthetics and the experience from clinical practice is very positive. Nevertheless, we have a lack of research evidence of the effectiveness of Kinaesthetics training for nursing staff and patients.

### Program theory and research plan

In order to make comprehensive evaluations possible, explicating the theory of a programme is helpful and often recommended. This is particularly true for complex interventions including exercise and motor learning [15,16]. Logical models can be used to form a programme theory.

According to Kellogg Foundation [17] we developed a logical model (Figure 1) connecting the following key elements of the intervention: assumption, inputs, activities, output, outcomes and impacts.

**Figure 1 F1:**
[figure not shown]
**Logical model of the Kinaesthetics training intervention for trial**.

The assumption is that Kinaesthetics training leads to a better movement competence of the nursing staff. A change in movement behaviour takes place with an individual specific movement support of the residents. This leads to a reduction in the subjectively perceived strain of the nurses and to a higher movement competence of the residents.

Using this model, a feasibility study is conducted. The study protocol will be prescribed in the subsequent sections.

### Reasons and objectives of the pilot trial and criteria of feasibility

Conceptualising the feasibility trial, we followed the tutorial Thabane and co-workers propounded [18]. The pilot is to cover several objectives on the staff level and on the resident level. The objectives are assigned to three main reasons for conducting a pilot: there are resources-oriented, scientific-oriented and process-oriented reasons. As used by another work group [19,20], main reasons, feasibility objectives and questions as well as criteria for feasibility success are summarised in Table 2. There are three resources-oriented criteria, five scientific-oriented criteria and two process-oriented criteria of feasibility success.

**Table 2 T2:** Resources, scientific and process criteria

Main reason for conducting a pilot study	Feasibility objective	Feasibility questions	Programme level	Criterion for feasibility success
Resources	Efforts for and completeness of recording data	Are the efforts for the participation in the trial reasonable? Is enough data obtained for a reasonable decision-making? Are the expenses justifiable?	residents	Less than 50% the residents would not participate again in the trial or drop out during the trial (RES_1)
			nurses	Less than 50% the nurses would not participate again in the trial or drop out during the trial (RES_2)
			both	Percentage of missing values below 20% for SOPMAS, below 50% for MOTPA (RES_3)
Scientific	Minimum effects (justifying further research)	Is Kinaesthetics mobilisation able to increase safety, participation and comfort as well as decrease pain for the residents?	residents	After staff training, at least 50% of the residents (a) perceive more safety, comfort and participation during mobilisation (at least 2 points, SCI_1) (b) perceive less pain during mobilisation (at least 2 points) SCI_2 (c) receive a higher median SOPMAS score of item "patient movement" (at least 1 point) (SCI_3)
		Is Kinaesthetics mobilisation able to decrease perceived physical strain and increase movement competence of the nurses ?	nurses	After staff training, at least 50% of the nurses (a) perceive less physical strain during mobilisation (at least 2 points) or increased Borg values can be ascribed to improvements in body perception (SCI_4) (b) receive a higher median SOPMAS score (at least 1 point) (SCI_5)
Process	Continuing Participation	Will residents and nurses be ready to participate in the trial over the full period?	residents	50% or less of the residents leave the programme on their own decision (i.e. not due to an adverse event or death (PRO_1)
			nurses	30% or less of the nurses leave the programme on their own decision (i.e. not due to an adverse event, PRO_2)

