#### Science-oriented feasibility

Immediately after each transfer recorded at T0, T1 and T2, the residents will be asked about the safety, comfort, pain and one's own participation during the transfer with a questionnaire. The scale ranges for pain from 0 = no pain to 5 = unbearable pain; for safety from 0 = very unsafe to 5 = very safe; for comfort from 0 = very uncomfortable to 5 = very comfortable and for participation from 1 = very low participation to 5 = very high participation. The feasibility criteria SCI_1 and SCI_2 will be calculated after data processing.

Immediately after every transfer recorded at T0, T1 and T2 the nurses will be asked about the subjectively perceived physical strain during patient transfer. The data will be collected with the Borg CR10 scale of perceived strain, with a scale from 0 = no strain at all to 10 = extreme strain after every patient transfer (SCI_4) [21].

The movement competence of the nurses will be measured with the SOPMAS Instrument (Structure of the Observed Patient Movement Assistance Skill) (SCI_5). It observes each nurse's individual performance and learning in patient transfer tasks and patient participation in locomotion activities with 4 items: interaction, patient's movement, the nurse's posture and movement, environment and auxiliary devices. The scale ranges from 1 = no skills to 5 = very good skills. All scale levels were given specific definitions, suited for patient transfer situations. The instrument was tested and compared with the Swedish DINO instrument [22] of which validity and reliability have been tested. The correlation was tested by the Pearson test and was good (r = 0.72), though there was a level difference. The highest level of the SOPMAS was missing in the DINO [12]. Video recordings of two transfers of each nurse, e.g. bed-wheelchair/chair-bed, transfer in bed (positioning) will be recorded at the measurement points at the baseline before training (T0), within one month after the basic course (T1) and within one month after the advanced course (T2). The feasibility criteria SCI_3 of the residents for the Item patient's movement and the score over all items SCI_5 for the nurses will be calculated after data processing.

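### SCI_2 counts a 2-point fall in pain over all residents, including those who start at 0 or 1 and cannot achieve it, so a failed criterion would not separate no effect from no room to improve

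*Protocol article*

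**What the plan says.** In the protocol article, section Reasons and objectives of the pilot trial and criteria of feasibility, Table 2 lists the scientific criteria for residents under the objective of minimum effects. SCI_1 reads "After staff training, at least 50% of the residents (a) perceive more safety, comfort and participation during mobilisation (at least 2 points, SCI_1". SCI_2, under the same 50% requirement, is that residents "perceive less pain during mobilisation (at least 2 points) SCI_2".

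The section Science-oriented feasibility defines the scales:
- Pain: "The scale ranges for pain from 0 = no pain to 5 = unbearable pain".
- Safety: "for safety from 0 = very unsafe to 5 = very safe".
- Comfort: "for comfort from 0 = very uncomfortable to 5 = very comfortable".
- Participation: "for participation from 1 = very low participation to 5 = very high participation".

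Setting and Sample lists the resident inclusion criteria. They cover need for mobility assistance, physical condition, German language, understanding of the study information and consent. None refers to pain or to a low score on the other scales. The same section expects 19 residents in the final sample and rules out inferential statistics.

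Primary outcome measures ties the outcomes to these feasibility criteria. The Discussion paragraph of the Abstract says of the ten criteria: "This will help to make rational decision on entering the next stage of the research program".

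**The concern.** A responder rule with a fixed minimum change needs participants who have room to change by that amount. SCI_2 sets the change at 2 points on a six-level scale and counts over all residents whatever their starting value. A resident with little or no pain at T0 is therefore a non-responder by construction. Nothing in Table 2 or the outcome sections removes such residents from the count or gives them another way to succeed. SCI_4, for the nurses, does have an alternative route, since a higher Borg value can count if it is ascribed to better body perception.

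The thresholds also differ in relative size. Two points are one fifth of the Borg range (2/10), two fifths of the pain, safety and comfort ranges (2/5) and one half of the participation range (2/4).

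What is at stake is the reading of the pilot. Training that helped most residents who have pain could still be recorded as missing the minimum effect on pain because of who was enrolled, and that record feeds the decision on the next research stage.

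**Working it through.** **Inputs.** From Setting and Sample: 22 eligible residents, about 5% refusal, 10% drop-out. From Table 2: a 2-point change in at least 50% of residents. From Science-oriented feasibility: the scale limits. The article gives no baseline scores, so the share f of residents starting at pain 0 or 1, and the share q of the remaining residents who improve by 2 points, are assumptions and are varied. One whole-number pain score per resident and time point is assumed.

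**1. The plan's own figure.** 22 × 0.95 × 0.90 = 18.81, which rounds to the stated 19.

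**2. Responders needed.** 0.5 × 19 = 9.5, so 10 (9/19 = 47.4% fails, 10/19 = 52.6% passes).

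**3. Who can respond.** A fall of 2 in pain is possible only from T0 values 2, 3, 4 or 5. A rise of 2 is possible only from 0 to 3 on safety and comfort, and from 1 to 3 on participation.

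**4. When SCI_2 is out of reach.** If 10 of 19 start at pain 0 or 1, at most 9 can respond, and 9 < 10. With all 22 residents, 11 responders are needed and 12 at the floor (54.5%) leave only 10.

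**5. How much harder it becomes below that point.** With k of 19 at the floor, the required response among the others is 10/(19 − k). For k = 4 this is 10/15 = 67%, for k = 8 it is 10/11 = 91%, and for k = 9 it is 10/10 = 100%.

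**6. Chance of meeting SCI_2.** Number of responders X ~ Binomial(19, (1 − f)q); the chance is P(X ≥ 10). The last column is the chance that 10 or more residents start at the floor.

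| Assumed f | q = 1.0 | q = 0.8 | q = 0.6 | Out of reach |
|---|---|---|---|---|
| 0.2 | 0.998 | 0.897 | 0.430 | 0.002 |
| 0.3 | 0.967 | 0.703 | 0.238 | 0.033 |
| 0.4 | 0.814 | 0.430 | 0.103 | 0.186 |
| 0.5 | 0.500 | 0.186 | 0.033 | 0.500 |
| 0.6 | 0.186 | 0.050 | 0.007 | 0.814 |

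For comparison, with nobody at the floor and q = 0.8 the success probability per resident is 0.8. That equals (1 − 0.2) × 1.0 in the first row, so the chance of passing is 0.998. With n = 22 and q = 0.8, the chances at f = 0.2, 0.4, 0.5 and 0.6 are 0.942, 0.509, 0.228 and 0.060, which is the same pattern.

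**7. SCI_1 under different readings.** If each of the three scales must rise by 2, one score of 4 or 5 blocks the resident. With 21% at 4 or 5 on each scale, the blocked share is 1 − 0.79³ = 50.7% if the scales are independent and 21% if they coincide fully. If the 2 points refer to the sum (range 1 to 15), only a T0 sum of 14 or 15 is blocked. Of the 6 × 6 × 5 = 180 possible score combinations, 180 − 4 × 4 × 3 = 132 are blocked under the each-scale reading and 4 under the sum reading. These counts compare the rules; they do not predict residents' scores.

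**The case against.** The best defence is that the all-resident denominator answers a fair question. If most residents have little pain during mobilisation, pain reduction is a weak reason for a larger trial in this population, and a failed SCI_2 says so. That stands, and it is a reason to keep the all-resident percentage. It does not help a reader of a failed criterion to tell whether pain was scarce or the training did nothing.

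The second defence is about remedy. In an uncontrolled pre-post study, restricting the count to residents with higher T0 pain selects for regression to the mean and makes passing easier: with 9 of 19 having room, 5 responders would exceed 50%. This also stands, so the restricted percentage should supplement the existing one and not replace it.

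The third defence is about weight. This is an exploratory pilot without inference, SCI_1 and SCI_2 are two of ten criteria, and no section says that failing one ends the programme. That limits the severity.

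Some stronger readings are tempting but not supported:
- A reader might infer that the rule demands a 2-point change from every resident. It asks for half of them, so up to 9 of 19 at the floor can be absorbed.
- A reader might infer that SCI_2 is bound to fail. With 20% at the floor and 80% response among the rest, it passes with probability 0.90, and the article gives no baseline data to say which case applies.
- A reader might infer that SCI_1 is the worse case. That needs the each-scale reading, which is natural but not stated. Even then, uniform baselines leave room on all three scales for 4/6 × 4/6 × 3/5 = 27% of residents only under independence; under full overlap the figure is 3/5 = 60%. Ratings by one person after one transfer are unlikely to be independent.

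**Conclusion.** The point holds for SCI_2 as a conditional weakness. The criterion is arithmetically unattainable once 10 of the expected 19 residents start at pain 0 or 1, and below that number each resident at the floor raises the response required from the others. At 80% response among residents with room, the chance of passing falls from 0.90 to 0.05 as the assumed floor share goes from 20% to 60%. These probabilities rest on assumed floor and response shares and on independent residents; the threshold of 10 rests only on the sample size and the scale.

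For SCI_1 the ceiling problem depends on a reading that the text does not settle. On a sum of the scales it largely disappears. What can be said firmly is that Table 2 does not state how the three scales combine.

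Severity: should-fix. The defect affects what a failed criterion can be taken to mean; the data to be collected are unaffected.

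**What to change.** Keep the 2-point and 50% figures and the percentage over all residents. Beside it, report:
- the percentage among residents with 2 points of room at T0 (pain at least 2; safety, comfort or participation at most 3);
- the number of residents at the floor or ceiling on each scale;
- the T0-to-T2 shift table for all residents.

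Report SCI_1 as one percentage per scale, and state in Table 2 that the 2 points apply scale by scale. If fewer than half of the residents have room on a scale, record that criterion as not evaluable (no room), not as evidence of no effect.

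The cost is a few words in Table 2 and some tabulation of data already planned; no new measurement is needed. The downside is a smaller denominator and regression to the mean in the restricted group, so its percentage should be read only together with the all-resident shift table.

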### Setting and Sample

Reasoning on sample and sample size for this pilot, we followed Thabane et al. [18], who recommend orientation at the feasibility criteria (see below). From this point of view, the present study does not allow sample size calculation. Consequently, inference statistics is not intended.

In order to avoid side effects, all eligible residents and all nurses in charge of them should be asked for participation in the study and offered Kinaesthetics training, respectively. On one hand, we considered a nursing home of typical size to yield a sufficient number of participants on the resident as well as the staff level. On the other hand, conducting the trial with two or more centres could be a waste of resources in case of feasibility problems.

The trial is conducted in a nursing home of the canton Basel, Switzerland, with 76 residents and 60 nursing staff. All seniors, who fulfil the inclusion criteria, will be asked to participate. According to the head nurse, 22 residents are eligible at the moment. For this feasibility study, 36 nurses who are regularly in charge are included. Based on the fact that usually about 5% of the persons asked do not wish to participate and 10% will drop out, the final sample size is estimated 19 residents.

Concerning the sample size of the nurses, it is assumed that about 5% of the persons asked that had the Kinaesthetics training would not like to participate and 10% will drop out. Consequently, the final sample size of the nurses is estimated about 31.

On the staff level, inclusion criteria are:

• participation in the Kinaesthetics training course during trial

• no Kinaesthetics training before

• informed consent

On the resident level, inclusion criteria are:

• needs assistance in mobility

• physical condition allows for participation

• can read and speak German

• is able to understand the study information

• informed consent

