#### Process-oriented feasibility

The reasons of residents and staff leaving the programme will be discriminated. Adverse events (AE) are considered in the process-oriented feasibility. Therefore, the whole number of drop-outs will be diminished by the drop-outs due to AE. Leaving the programme on one's own decision should be 50% or less for the residents (PRO_1), and 30% or less for the nurses (PRO_2).

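### SCI_1 to SCI_3 count only residents who improve and treat unchanged and worsened residents alike, so a minimum effect can be declared while residents are worse off on average

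*Protocol article*

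**What the plan says.** Table 2 (section Reasons and objectives of the pilot trial and criteria of feasibility) sets three resident-level criteria under the objective of minimum effects that justify further research. All three share one stem, "After staff training, at least 50% of the residents", followed by a margin of improvement:

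- SCI_1: "perceive more safety, comfort and participation during mobilisation (at least 2 points, SCI_1".
- SCI_2: "perceive less pain during mobilisation (at least 2 points) SCI_2".
- SCI_3: a gain of at least 1 point in the resident's median score on the SOPMAS item for patient movement.

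The section Science-oriented feasibility gives the scales, for example "The scale ranges for pain from 0 = no pain to 5 = unbearable pain", and says that the criteria are calculated after data processing. Neither place limits the share who worsen, sets worsened residents against improved ones, or asks for a favourable average change.

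These criteria carry weight. The section Primary outcome measures ties the outcomes to them, the Abstract says that the ten criteria are fixed before the trial to support the decision on the next stage, and Setting and Sample says that no inferential statistics are intended.

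**The concern.** A rule that counts only improvement gives the same score to a resident with no change and a resident whose pain rises by 3 points. The starting level makes this relevant for pain: a resident at 0 or 1 at T0 cannot fall by 2 points but can rise, and the rule does not look in that direction.

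The other criteria do not measure it either. Under Process-oriented feasibility, "Adverse events (AE) are considered in the process-oriented feasibility", but only by subtracting drop-outs due to adverse events from the drop-out count. A resident who stays in the study with more pain is not seen there. The only criterion that mentions a change in the unfavourable direction is SCI_4, for the nurses, and it does so to allow higher strain ratings under a condition.

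At stake is the meaning of a pass. A technique that helps some residents and makes transfers worse for others could be recorded as showing minimum effects even when the average resident is worse off.

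**Working it through.** **Inputs from the protocol article.** Setting and Sample: "According to the head nurse, 22 residents are eligible at the moment", about 5% refuse and 10% drop out, and the final sample is put at 19. Table 2: share of at least 50%; margin of 2 points for SCI_1 and SCI_2 and 1 point for SCI_3. Science-oriented feasibility: pain is scored 0 to 5.

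**The plan's own figure.** 22 × 0.95 × 0.90 = 18.81, which rounds to 19 as stated.

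**Residents needed for a pass.** Half of 19 is 9.5, so 10 must improve: 10/19 = 52.6%. That leaves 9, and 9/19 = 47.4%.

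**Mean change in pain.** Let 10 residents improve by exactly 2 points and 9 worsen by d points. The mean change is (−2 × 10 + 9d)/19.

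| d | Mean change, n = 19 |
|---|---|
| 2 | (−20 + 18)/19 = −0.11 |
| 3 | (−20 + 27)/19 = +0.37 |
| 4 | (−20 + 36)/19 = +0.84 |
| 5 | (−20 + 45)/19 = +1.32 |

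The mean is unchanged at d = 20/9 = 2.22. If all 22 eligible residents were analysed, 11 would improve and 11 could worsen, and (−22 + 11d)/22 gives 0.00, +0.50, +1.00 and +1.50 for d = 2 to 5.

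**A case that fits the scale.** Ten residents go from 3 to 1 and nine from 0 to 3. SCI_2 is met. Mean pain goes from 30/19 = 1.58 to 37/19 = 1.95, a rise of 0.37.

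**Fewer worsened residents can suffice.** With 10 improving by 2 and the rest unchanged, 7 worsening by 3 points give (−20 + 21)/19 = +0.05, and 5 worsening by 5 points give (−20 + 25)/19 = +0.26.

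**SCI_3.** Ten residents at +1 and nine at −2 meet the criterion with a mean change of (10 − 18)/19 = −0.42. With nine at −1 the mean is (10 − 9)/19 = +0.05.

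**Could RES_1 catch it?** RES_1 requires that fewer than 50% of residents drop out or say they would not take part again. If all nine worsened residents said so and nobody dropped out, 9/19 = 47.4% would still pass.

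**The case against.** The strongest reply is that SCI_1 to SCI_3 ask whether the approach can help enough residents to justify more research. A responder threshold answers that, and every such threshold pools unchanged with worsened cases. The document does not contradict itself here. That is fair, and it makes this an improvement to the rule, not the correction of an error.

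Other replies limit how far the point goes:

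- A reader might infer that passing SCI_2 alone sends the programme to a controlled trial. The Abstract does not support that. Ten criteria together inform the decision, effect estimates are also to be used, and pain is recorded at T0, T1 and T2, so the pattern could be noticed. What stands is that no pre-set criterion would have to fail because of it.
- A reader might infer that nothing else could register worse transfers. RES_1 could, indirectly, since residents with bad experiences may decline to take part again and its drop-out count has no exclusion for adverse events. The working shows that it need not.
- A reader might infer that worsening by the margin is enough to raise mean pain. It is not: at exactly 2 points in all nine, the mean falls by 0.11.
- Residents who start at pain 0 or 1 stay in the denominator and cannot respond, which makes SCI_2 hard to meet and a misleading pass less likely. This stands as a matter of likelihood, not of what the rule allows.
- A fixed cap on the worsened share, such as 20%, would have no basis in the document. In an uncontrolled pre-post study with 10 months between the courses, some residents may decline for reasons unrelated to handling. This stands, and no cap is proposed.

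**Conclusion.** The point holds as a statement about what the rule permits. SCI_1 to SCI_3 can be met with up to 9 of 19 residents (47.4%) worse, and for SCI_2 mean pain then rises if those nine worsen by more than 2.22 points on average (+0.37 at 3 points each). Even where the mean does not rise, 10 improved against 9 worsened by the same margin is a net difference of 1/19, or 5.3 percentage points, and the criterion still counts as met.

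The figures assume 19 analysed residents, improvement of exactly the margin in the minimum number needed, and, for the threshold of 2.22, worsening in all the others. Nothing in the document makes that pattern likely, and it should not be read as a prediction of harm. The pilot remains sound; its rule for declaring a minimum effect is looser than it needs to be.

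**What to change.** In Table 2, call each of SCI_1, SCI_2 and SCI_3 met only if (1) at least 50% of residents improve by the stated margin and (2) the mean change across the same residents, over the same comparison, is in the favourable direction. For SCI_1, apply the second condition to safety, comfort and participation separately.

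When the next stage is decided, show the share worsening by the same margin beside the improved share. This matters because the mean condition alone would let through the case of nine residents worsening by exactly 2 points (mean −0.11).

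No numerical cap on the worsened share is needed. If the sponsor wants one, it is for the sponsor to choose and justify it before the post-training data are seen.

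The cost is one added clause and slightly stricter criteria. All the data are already collected.
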